## Abstract

**Background:**

Patients with end-stage renal disease undergoing hemodialysis face substantial challenges in adhering to complex therapeutic regimens, significantly impacting morbidity, mortality, and quality of life. While conventional educational methods offer some benefit, interactive digital tools may yield deeper engagement and sustained behavioral change.

**Objective:**

This study assesses and compares the impact of interactive and conventional video-based education, as well as usual care, on patient activation, treatment adherence, and inter-dialytic weight gain in individuals undergoing hemodialysis.

**Methods:**

A three-arm, parallel-group, randomized clinical trial will be conducted in three academic hospitals in Tehran, Iran. A sample of patients will be enrolled and distributed into one of three categories: (1) interactive video education, (2) conventional video education, or (3) typical nurse-led education. The 13-item Patient Activation Measure will be used to measure the primary outcome of patient activation. Secondary outcomes will encompass treatment adherence, as measured by the End Stage Renal Disease Adherence Questionnaire, and inter-dialytic weight gain. Evaluations will occur at baseline, immediately post-intervention, and at 1- and 3-month follow-up intervals. Data will be analyzed using intention-to-treat principles with mixed-effects modeling.

**Discussion:**

This trial is among the first to rigorously compare interactive and conventional video education in a dialysis population. Findings may inform scalable, cost-effective strategies for improving self-management and adherence in patients with end-stage renal disease. This protocol was registered prospectively at ClinicalTrials.gov (Registration No. NCT07099326) on July 31, 2025. The National Research Ethics Committee also approved the study with the ethics code: IR.SBMU.PHARMACY.REC.1404.067.

## Introduction

Chronic kidney disease (CKD) is a significant global health risk factor and is more prevalent in people over 60 years old [1]. CKD denotes a state of impaired renal function characterized by the loss of over half of normal kidney function [2], and is identified by indications of kidney damage or an estimated glomerular filtration rate (eGFR) below 60 mL/min/1.73 [3]. Based on eGFR values, CKD patients are stratified into five distinct stages [4]. Advanced stages (3–5) of the disease significantly affect daily activities, nutritional status, fluid and electrolyte balance, and overall health, potentially leading to uremic syndrome and mortality if untreated [5]. End-stage CKD, also termed End-Stage Renal Disease (ESRD), involves an irreversible decline in kidney function, causing continuous dialysis or kidney transplantation for survival [6].

According to 2016 statistics from Iran, there were over 55,000 documented CKD patients, including 27,500 receiving hemodialysis (HD) and 1,600 receiving peritoneal dialysis (PD) [1]. Further research shows that the number of CKD patients in Iran rises by approximately 15% each year [1,7]. At present, HD represents the predominant treatment modality for ESRD within the nation [8]; however, individuals undergoing HD encounter challenges, such as the imperative of strict dietary adherence to mitigate cardiovascular complications [9]. For an HD program to be implemented effectively, four critical aspects must be followed: diet, medication, fluid restriction, and consistent dialysis session attendance [1].

As demonstrated by their behavior [10], the patient’s active participation in treatment, adherence to recommendations, and receipt of care services define treatment adherence. Multiple studies indicate that patients undergoing HD show suboptimal adherence to treatment plans, which can accelerate disease progression and increase the risk of emergency hospitalizations [11–13]. As biochemical and physiological indicators, Kt/V and inter-dialytic weight gain (IDWG) are used to assess dialysis adherence [10,14–16].

To improve adherence and self-management among patients afflicted with chronic illnesses, the concept of “patient activation” was developed, measuring the patient’s knowledge, skills, and confidence in managing their own health via the PAM (Patient Activation Measure) tool [17]. Increased activation shows a relationship with optimal treatment consequences, a reduction in unwarranted emergency care utilizations, and reduced rates of hospital re-attendance [18]. Patient activation can be modified and is influenced by elements including age, gender, socioeconomic standing, CKD stage, disease duration, and existing comorbidities [17,19]. This concept is classified into four levels: level 1, at which the patient experiences being overwhelmed by the disease and a lack of motivation; Level 2, where the patient has begun self-care but lacks adequate knowledge and confidence; At the third level, the patient seeks to maintain and improve health, yet lacks the abilities and beliefs, and at level 4, the patient shows sufficient knowledge and skill for actively managing their disease [20]. Research shows a direct correlation between the degree of patient engagement and adherence to dietary and fluid limitations; diminished engagement may cause non-adherence and subsequent weight increase between dialysis treatments [21,22].

The difference between a patient’s weight at the close of a dialysis session and the subsequent session’s beginning, known as IDWG, is deemed a meaningful measure of fluid regulation and, secondarily, patient adherence to fluid restrictions and clinical factors [14]. Despite international guidelines recommending that IDWG be maintained below 4–4.5% of dry weight, many patients cannot adhere to this restriction and consequently experience excessive weight gain between dialysis sessions [16,23]. Many investigations have shown that heightened IDWG correlates with an elevated incidence of mortality and cardiovascular morbidity, encompassing left ventricular hypertension and unfavorable cardiovascular and cerebrovascular occurrences [24–26]. Excessive weight gain also results in a higher frequency of dialysis treatments, which considerably impairs one’s quality of life (QoL) and substantially elevates healthcare expenses [27,28]. Significant impediments to compliance with dietary and fluid limitations encompass an insufficient understanding of fluid balance, diminished incentive, and pre-existing pathological states affecting residual renal performance and fluid elimination rates [27,29].

Educational training forms an essential component of nursing practice, executed via various modalities [30]. Conventional video-based education is one such method, where patients view pre-recorded videos and receive information on the topic in a one-way manner [31]. Research shows that these videos may enhance patient comprehension of disease-related care and ease pre-treatment anxiety [31,32]. An alternative approach is education delivered via interactive video. Patient engagement with the material through interactive questions, virtual simulations, and immediate feedback promotes deeper learning and improves motivation to comply with treatment recommendations, in contrast to passive video observation [33,34].

Conventional video education reliably increases patient knowledge in chronic illness settings, including preliminary studies in dialysis, but systematic reviews report that knowledge gains do not consistently translate into improved clinical or utilization outcomes; the specific educational features that drive behavior change are not well defined. Importantly, there is a paucity of rigorous randomized clinical trials (RCTs) in the hemodialysis population that compare interactive video formats (with real-time feedback, embedded assessments, or simulated practice) against passive, conventional videos for their effects on patient activation and objective adherence measures [35]. Interactive, adaptive educational modalities have improved engagement and some behavioral or clinical outcomes in other chronic-disease contexts, and patient activation (measured by PAM) is a promising mediator of sustained self-management; however, the relationship between activation-focused, interactive education and dialysis outcomes (e.g., Kt/V, session attendance, and IDWG) remains inadequately tested [36]. Because elevated IDWG is consistently associated with greater cardiovascular risk and mortality in dialysis cohorts, an RCT comparing interactive vs conventional video education is timely and necessary to inform evidence-based educational strategies that aim to change behavior and improve clinically meaningful endpoints. Therefore, designing an RCT comparing the effectiveness of interactive video education with that of passive video regarding patients’ activation variables, treatment adherence, and weight changes may lead to more effective solutions and improvements in the quality of care for these patients.

## Method

This protocol has been developed in accordance with the SPIRIT 2025 (Standard Protocol Items: Recommendations for Interventional Trials) guidelines to ensure transparency, completeness, and reproducibility of the trial design (S1 Table) [37].

### Trial design

This study is designed as a three‑arm, parallel‑group RCT with a 1:1:1 allocation ratio. Hospitals (Shohada‑ye Tajrish, Taleghani, and Imam Hossein) are the desired study settings. The trial will be conducted within a superiority framework to compare the effectiveness of the educational interventions across the study arms.

### Setting

Participants will be recruited from inpatient units in three hospitals—Shohada-ye Tajrish, Taleghani, and Imam Hossein—all affiliated with Shahid Beheshti University of Medical Sciences in Tehran, Iran. Recruitment will occur within hospital clinics and wards to ensure appropriate access to the target population.

### Sample size

Due to the absence of previous studies closely matching the design and interventions of the present trial, the sample size calculation will be based on data obtained from a preliminary pilot study that the research team will conduct. A pilot study will be conducted in the same dialysis units as the definitive three-arm trial. It aims to (1) estimate parameters required for sample-size calculation (primary-outcome SD), (2) assess recruitment and retention rates, (3) measure patient adherence and provider fidelity, (4) evaluate methodological contamination, and (5) identify operational or data-quality problems.

The selection of this approach ensures that the sample size possesses sufficient statistical power to identify clinically relevant differences between groups, taking into account the unique features of both the study population and the interventions.

Participants will be screened consecutively using the same inclusion/exclusion criteria as in the primary protocol, provide informed consent, and be randomized to one of three arms. The intervention principles, outcome instruments, and timepoints will be identical to those in the definitive trial. For feasibility-only objectives, approximately 12 participants per arm (36 total) will be recruited [38]; if variance estimation is required, around 35 per arm (105 total) will be targeted [38].

A pilot report will document parameter estimates and operational findings. Pilot outcomes include: Standard Deviation (SD) and 95% Confidence Interval (CI) of the primary outcome, recruitment and retention proportions, adherence categories, fidelity scores from structured checklists, contamination based on self-report and digital access logs, and data-quality indicators (missing data, questionnaire burden, technical issues).

Pilot estimates will inform the definitive sample size, attrition-adjusted recruitment targets, and possible design modifications if contamination is substantial. Any changes to the main trial will be justified, approved, and reported. The sample size will be estimated using the pilot data, with a significance level of 0.05 (two-sided) and a statistical power of 80%. The total estimates will be allocated equally across the three study groups. By relying on pilot data without prior literature, the study design ensures methodological rigor and optimizes resource use while maintaining sufficient power to address the primary research objectives.

### Eligibility criteria

Eligible participants will be required to meet all of the following criteria: (1) willingness to participate in the study, (2) literacy in reading and writing, (3) alertness and orientation to time, place, and person sufficient to respond to questions, (4) no history of auditory or visual impairments, (5) absence of cognitive disorders, (6) ownership of a personal mobile device or equivalent capable of running interactive video applications and ability to use it, (7) no current use of psychoactive medications, (8) confirmed diagnosis of CKD by a nephrology specialist with an active medical record in the dialysis unit, and (9) age between 18 and 65 years. Participants will be withdrawn from the study upon meeting any of the following exclusion criteria: (1) voluntary withdrawal from the study at any time, (2) failure to receive and engage with the assigned video interventions, (3) death of the participant, and (4) transfer to a healthcare facility affiliated with universities other than Shahid Beheshti University of Medical Sciences.

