#### Phase 1: Conventional video-based instruction (10 × 30-minute modules).

Participants will access the secured learning platform at https://spotplayer.ir/ to view ten pre-recorded video modules detailing ESRD pathophysiology and alternative treatment modalities. One 30-minute module will be released daily. Videos will be streamed in their entirety without interactive elements; the instructor will oversee module completion and address any technical queries but will not interject during playback.

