### Control group (Usual care)

Participants in the control arm will receive the standard educational practices routinely implemented at each site. Specifically, this will include:

**Nurse-led education:** Registered nurses in the dialysis unit will provide face-to-face instruction on disease management and self-care behaviors.**Educational pamphlets:** Participants will be given institution-approved printed materials covering key aspects of ESRD and alternative therapies.**Nurse follow-up:** A dedicated follow-up nurse will provide regular monitoring, either in person or via telephone, to reinforce educational information, address inquiries, and assess adherence to suggested self-care methods.

All procedures will be conducted according to each hospital’s established protocols and within the time-frame of the three-hour educational session allocated to the intervention arms (Fig 2).

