### Allocation concealment

Assignments will be implemented through a centralized, password-protected web-based randomization system to maintain allocation concealment and prevent selection bias. The allocation will only be revealed after participant eligibility and baseline assessment have been completed. If a central system is unavailable, sequentially numbered, opaque, sealed envelopes, prepared by the independent statistician, will be used following best practices [39].

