### Plans to promote participant retention and complete follow-up

To maximize retention and reduce missing data, the following strategies will be implemented: Research staff will maintain monthly contact with participants via phone or messaging to encourage continued participation and address any technical or logistical challenges. Also, participants will receive automated reminders (SMS or calls) for each video session and follow-up assessment point. Assessments will be conducted during routine dialysis sessions to reduce participant burden. In the event of participant discontinuation or deviation from the intervention protocol, all primary and secondary outcome data will be gathered at the defined follow-up intervals. Reasons for discontinuation or protocol non-adherence will be documented through structured exit interviews. All outcomes will be analyzed under the intention-to-treat principle. Missing data (overall percentage, distribution across arms, and patterns) will be carefully described. If the amount of missing data on the primary outcome is very low (≈≤5%) and there is no evidence of systematic or differential missingness between arms, a complete-case analysis may be reported as the primary analysis, with multiple imputation (MI) used as a sensitivity check. MI will be the primary approach if missingness is higher or shows evidence of association with treatment arm or baseline covariates [44–46]. Imputation models will include all outcome time-points, treatment allocation, baseline covariates, and auxiliary predictors. Appropriate conditional models will be applied by variable type (predictive mean matching for continuous, logistic/multinomial/ordinal regression for categorical). At least *m* = 20 imputations will be generated (increasing *m* if the fraction of missing information is large). Chain convergence will be checked, and each imputed dataset will be analyzed with the pre-specified mixed model (or GEE for longitudinal outcomes). Estimates will be pooled using Rubin’s rules. Robustness will be examined using complete-case analyses, pattern-mixture approaches, and delta-adjustment (tipping-point) sensitivity analyses. Implementation and diagnostics will be conducted in R.

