### Statistical analysis

The baseline characteristics will be summarized using descriptive statistics (mean ± SD, frequency, and percentage). Primary and secondary outcomes will be analyzed using longitudinal data analysis methodologies, accommodating repeated measures collected at four time points (baseline, immediate post-intervention, one-month, and three-month follow-up) and across three intervention groups. Depending on the attributes and distribution of the dependent variables, consideration will be given to both mixed models for repeated measures (MMRM) and generalized estimating equations (GEE).

MMRM will be applied to model continuous normally distributed outcomes, incorporating fixed effects for group, time, and their interaction, with an appropriate covariance structure to account for within-subject correlations. GEE will be used as an alternative approach, particularly for outcomes with non-normal distributions or when robust population-averaged effects are of interest. MMRM and GEE will be chosen based on model fit and assumptions.

Analyses will be conducted under the intention-to-treat principle. Missing data will be addressed using multiple imputations, assuming they are randomly missing. Effect measures, CI, and a significance level of p < 0.05 will be reported. Adjusted analyses may include relevant covariates, with the primary analysis specified accordingly.

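### The eligibility section withdraws video non-engagers from the study after randomisation, which only the two video arms can trigger and which contradicts the planned follow-up and intention-to-treat analysis

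*Protocol article*

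**What the plan says.** Eligibility criteria, after the inclusion list: "Participants will be withdrawn from the study upon meeting any of the following exclusion criteria". The second of the four criteria is "failure to receive and engage with the assigned video interventions". The other three are voluntary withdrawal, death, and transfer to a facility outside the university. No threshold for engagement is given there.

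Allocation concealment: "The allocation will only be revealed after participant eligibility and baseline assessment have been completed".

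Control group (Usual care): "Participants in the control arm will receive the standard educational practices routinely implemented at each site". This consists of nurse teaching, pamphlets and nurse follow-up, with no video.

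Plans to promote participant retention and complete follow-up: when a participant discontinues or deviates from the intervention protocol, "all primary and secondary outcome data will be gathered at the defined follow-up intervals", and "All outcomes will be analyzed under the intention-to-treat principle". Multiple imputation is primary when missingness is more than very low or is associated with arm or baseline covariates. Pattern-mixture and tipping-point analyses are planned to examine robustness.

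Statistical analysis: "Analyses will be conducted under the intention-to-treat principle". Missing data are to be multiply imputed on the assumption that they are missing at random.

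Strategies to mitigate instructor bias, workshop imbalance, and participant adherence: a participant must complete all ten video modules to count as treated to plan. Those who fall short go into a separate category and are not described as leaving the trial.

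**The concern.** The withdrawal rule acts after randomisation, ends study participation and not merely the intervention, and has no counterpart in usual care. A usual-care patient who ignores the nurse and the pamphlets stays in the study. A video patient who ignores the videos does not.

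The primary outcome is patient activation, which the Introduction describes as knowledge, skills and confidence in managing one's own health. Patients who do not engage with self-management education plausibly have lower activation at follow-up than those who do, beyond what baseline predicts. Losing them from the video arms alone would tilt both video-versus-usual-care contrasts towards video.

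The analysis cannot fully repair this. Imputation under missing at random fills the gaps largely from engaged participants in the same arm. The pattern-mixture and tipping-point analyses would help to expose the problem, but they are sensitivity checks and leave the primary estimate as it is. Outcomes never collected because a site treated the participant as withdrawn cannot be recovered later.

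**Working it through.** **Textual check**

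1. *When can the rule apply?* A video is assigned only once allocation is revealed, which follows eligibility and baseline assessment. Failure with an assigned video is therefore always a post-randomisation event.
2. *Who can trigger it?* The interactive and conventional video arms can. Usual care contains no video and cannot. The other three criteria apply to all arms.
3. *What follows?* Eligibility criteria: the participant leaves the study. Retention section: outcomes are still collected and analysed by intention to treat. Adherence section: the participant is classified as not having been treated to plan, which presupposes continued participation. A site cannot both withdraw a non-engager from the study and collect that person's three-month Patient Activation Measure (PAM). Nothing says which section governs.

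**Size, as an illustration only**

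The protocol states no definitive sample size, SD, target difference or non-engagement rate, so there is no figure of its own to reproduce.

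Inputs:
- Two-sided significance level 0.05 and 80% power (Sample size).
- Effect size g = 0.522, quoted in the Discussion from a meta-analysis. It is not a design input and serves here only to obtain a plausible arm size.
- p, the share of a video arm withdrawn and not followed: assumed 10%, 20%, 30%.
- d, the follow-up PAM deficit of those withdrawn relative to those retained, in SD, not predicted by baseline: assumed 0.3, 0.5, 0.8.
- No true effect of video.

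Arm size: by the normal approximation, n = 2 × (1.96 + 0.842)² / 0.522² = 57.6. The two-sample t-test gives 58.6, rounded up to 59 per arm.

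Bias: the full-arm mean is the retained mean minus p × d, so analysing only those retained overstates the arm by p × d.

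Standard error: SE = √(1/59 + 1/(59(1 − p))).

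False-positive rate: P(|Z + bias/SE| > 1.96).

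| p | d | Bias (SD) | SE | Bias/SE | False-positive rate |
|---|---|---|---|---|---|
| 10% | 0.3 | 0.03 | 0.189 | 0.159 | 3.58% + 1.71% = 5.3% |
| 20% | 0.5 | 0.10 | 0.195 | 0.512 | 7.38% + 0.67% = 8.1% |
| 30% | 0.8 | 0.24 | 0.203 | 1.183 | 21.86% + 0.08% = 21.9% |

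Against g = 0.522, the middle bias is 0.10/0.522 = 19% and the largest is 0.24/0.522 = 46%.

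If the retention section is followed, so that every randomised participant is followed and analysed in the assigned arm, p is zero for this purpose and so is the bias. If non-engagers are withdrawn and then imputed, the same formula applies with d read as the deficit that the imputation model does not explain. Good auxiliary predictors would reduce it.

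**The case against.** The strongest reply is that the protocol already answers the problem. The retention section covers exactly this situation, two sections commit to intention to treat, and no sentence removes withdrawn participants from the analysis set. A reader might infer from the eligibility section that the trial will in fact compare engaged video users with all usual-care patients. The documents do not support that, because it happens only if the withdrawal rule overrides the retention section. What stands is the contradiction: site staff reading the withdrawal list are told to end participation, and the text gives them no reason to do otherwise.

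The missing-data plan is also better than missing at random alone. It makes multiple imputation primary when loss is related to arm, allows auxiliary predictors, and adds pattern-mixture and tipping-point analyses. That lowers the risk but does not correct the primary estimate.

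The direction of bias is plausible but undocumented. Technical failure to receive a video also triggers the rule and need not signal low activation.

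Two further inferences are tempting and should not be drawn. One is that low engagement would be easier to detect in the interactive arm, because its responses and quizzes are recorded while the conventional videos are passive ("Videos will be streamed in their entirety without interactive elements"). However, viewing durations and the start and completion times of each session are logged on the video platform, and the conventional-arm instructor oversees module completion. With no threshold for engagement stated, unequal detection is speculation. The other is that counting non-engagers as attrition harms the trial by inflating the recruitment target. A larger target would add power and does not threaten validity.

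**Conclusion.** The contradiction is certain. The eligibility section withdraws video-arm non-engagers from the study, while the retention and adherence sections keep them in it. The bias is conditional: zero if the retention section is followed, and probably in favour of video over usual care if the withdrawal rule is applied.

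The illustrated range, 0.03 to 0.24 SD with a false-positive rate of 5.3% to 21.9%, rests wholly on assumed values of p, d and arm size. The low end is negligible and nothing in the document favours one end over the other. It shows that the choice between the sections can matter, not how much it will. The wording should be settled before follow-up begins, because it decides whether the outcome data will exist.

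**What to change.** Delete the second criterion, on non-receipt and non-engagement, from the withdrawal list in Eligibility criteria. Record such participants as deviating from or discontinuing the intervention while remaining in the study. State that the retention section governs: PAM, the End-Stage Renal Disease Adherence Questionnaire and inter-dialytic weight gain are collected at every planned visit, and each participant is analysed in the randomised arm. Use the platform logs only to describe adherence, to apply the existing per-protocol classification, and as auxiliary predictors in the imputation model.

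The cost is a short amendment. Follow-up of these participants is already planned. The one downside is that the estimated video effect may be slightly smaller, since non-engagers stay in the comparison.
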